#### **D.6. c. Determining the monthly incidence of child diarrhea in both arms of the study**

This task will be achieved by monitoring diarrheal morbidity in a cohort of 30 study children (from different households) in each of the 22 village-clusters, (total of 330 children in each study arm, 660 children total). We will obtain information on our main outcome, cluster(village)-level incidence rates of diarrheal episodes through two monitoring procedures for the entire 12 month follow-up period:

- 1.) Morbidity diaries: Morbidity calendars will be kept by mothers/caretakers of the children. The use of morbidity diaries or 'illness calendars' has recently been reviewed and their usefulness and validity confirmed in prospective studies on child health (Goldman et al. 1998). The mother/caretaker will be given a simple morbidity calendar to keep daily records of the child's morbidity status. This chart was pre-tested among 11 households in our pilot study in Mizque and the graphical illustrations proved culturally valid. The number of bowel movements (from sunrise to sunset), color and consistency of the stool as well as specific symptomatic features of the diarrheal episode were recorded using colored stickers (Appendix J). The usefulness of the tools for monitoring child health has been taken up enthusiastically by mothers and quantitative data on diarrhea frequency were collected (Jul-Aug.2002) in one village.
- 2.) Weekly home visits by community-based fieldworkers. Specific inquiries about the occurrence of a diarrheal episode using a standardized questionnaire will be made at the time of the fieldworker's weekly home visit. We will use vernacular terms of locally defined diarrheal illnesses derived from ethnographic pilot investigations in Mizque. For each of those illnesses, we will assess indicators for diarrhea as objectively as possible. This includes frequency of bowel movements and the presence of other symptoms (fever, vomiting, dehydration). Signs of dehydration will be assessed by both the number of urinations in last 24 hours as well as by capillary refill time. The different outcomes of the study (see below) will, thus be obtained by 52 measurements during the 12 months of follow-up. The assessment of the impact of SODIS on diarrheal morbidity will be obtained from cluster-level (villages) and individual (child) level outcome measures:

Village-level outcome measures: a *cluster(village)-level incidence rate* will be obtained by dividing the total number of diarrheal episodes in a cluster (village) by the total observation time of the study children in each village. This represents an incidence density measure. Similarly, the *mean number of episodes* of diarrhea per village-cluster will be compared among study groups.

Child-level outcome measures: the *total number of days with diarrhea*, and the *mean duration of diarrhea*, and the *number of visits to a healthcare provider* will be used for a child-level analysis of the intervention effect. The impact of

SODIS in terms of reduction of severe diarrheal episodes with blood, and/or fever or persistent episode (>14 days) will be assessed in a separate analysis.

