**Project Summary**

More than one third of the population in rural and in peri-urban areas of developing countries has no access to sufficient or clean drinking water free of pathogens. Thus, waterborne gastroenteritis remains a major infrastructural and public health problem particularly, as effective treatment (filtration, chlorination, treatments plants) is often beyond financial means or environmental resources used for water purification (fire-boiling, burning carbon-based fuels) become scarce in those communities. In this context solar disinfection of drinking water is especially appealing using a combination of irradiation by direct sunlight and solar heating to kill the water-borne pathogens in contaminated drinking water. To date, the efficacy of the SODIS technology as a home-based, low-cost intervention to provide safe drinking water in low income countries is well established, and a large-scale promotion and dissemination program is under way in seven Latin American countries. The principal objective of this study is to evaluate the effectiveness of home-based solar water disinfection (SODIS) in reducing the burden of gastrointestinal illness in children under 5 years in rural villages participating in a country-wide Bolivian SODIS program. We will conduct a community (cluster)-randomized controlled trial following a cohort of children <5 in each community. Totally, 22 communities will be selected from among those districts designated by the country-program to receive the SODIS intervention. A pair-matched design will be employed where communities are first ranked according to their baseline incidence of diarrheal disease and the intervention then assigned within each of the 11 consecutive pairs of communities randomly to one of them. In each cluster, 30 children (660 in total) will be enrolled and followed up for 12 months. Data on diarrheal illness will be obtained from morbidity diaries kept by mothers and validated through weekly home visits. Stool samples will be collected during the baseline morbidity surveys and at times of a diarrheal episode in a child during follow-up. Water quality monitoring of raw water sources used for drinking water and of water samples after treatment with the SODIS device will be conducted systematically. Mothers of participating children will be interviewed at baseline and during the trial with regard to current water use, behavioral and environmental exposures of their child in the home and within the community. This study will specifically estimate; i.) how much of the efficacy of the SODIS technology established in laboratory experiments and in two tightly controlled phase-III trials can be retained as effectiveness i.e. under program conditions, ii.) the preventive fraction of all-cause child-diarrhea attributable to SODIS. In addition, pathogen-specific attributable risks of diarrheal illness will be calculated. The project is organised by the University of California, Berkeley, with its substantial experience in water intervention trials in US and it benefits from the tradition of North-South collaboration in public health research of the Swiss Tropical Institute, Basel, Switzerland. It is run jointly with the Universidad Mayor de San Simon which coordinates the Bolivian SODIS program..

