## C.2. Development of data collection instruments

Draft data collection instruments for the first submission of this proposal were developed based on various forms from several previous field studies in Zimbabwe, Tanzania and more recently from our study on SODIS in

Bangladesh and in Bolivia. Final drafts of these instruments in English are currently developed incorporating findings of the 2002 study (Appendix F-2). These instruments will be submitted for IRB clearance at all study sites before their use in this trial. However, actual interviews are performed using the instruments written in local Quechua language (previous versions from 2001 in Appendix J). They were translated into the local Quechua language and back-translated to English to ensure accuracy of the translation and clarity of contents. They include a screening and enrolment questionnaire and five principal data collection instruments: i) a questionnaire for baseline assessment of socio-demographic characteristics of the study child and household including questions on water management and use; ii) a weekly observational protocol to monitor water, hygiene or sanitary conditions at the community and in the household; iii) a weekly follow-up questionnaire on gastrointestinal symptoms to be administered by the community-based field staff; iv) a questionnaire for assessing exposure risks at four different times during the study period; v) We also developed an illustrated household morbidity diary for self-administration and recording of diarrheal illness for the study child and household members. This serves to validate our weekly diarrheal morbidity assessment through a maternal interview. Similar participatory instruments have been successfully used previously (Stanton and Clemens 1987) and their validity and use in the application of diarrheal disease research has been advocated recently (Goldman et al. 1998, Kalter et al. 1991). A similar tool has also been successfully applied by our group in a recent study on gastrointestinal illness in HIV population in the US (Colford et al. Appendix G). These instruments have been shown to be at the same time appropriate for the use by locally trained personnel and capable of measuring the outcomes and exposures of interest. Questionnaires were developed using English templates from previous studies and were then discussed with the local Bolivian field team. Interviewers and data collectors were trained during a one-week workshop organized locally. Overall, our pilot study and previous experience demonstrated that with adequate personnel and with the instruments that we developed, data collection was complete, operationally and logistically feasible to obtain in a rural setting and over a prolonged period of time.

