## D.4. Definition of diarrhea (principal outcome)

An episode of diarrhea will be defined in this activity and throughout the trial as a 24 hours period with three or more non-bloody loose or liquid motions, or one or more bloody, loose or liquid motions and three diarrhea-free days between a new onset. This is in concordance with the WHO recommendations and recent research (Ahmed et al. 1994, Aziz et al. 1990, Morris et al. 1994) and allows the comparison with other studies on diarrheal diseases in developing countries. Concepts of diarrheal illness and disease differ within and between cultures (Pitts et al. 1996, Weiss 1988). For example, a nutritional program in Honduras neglected to use word 'empacho' in their instructions for correct feeding practices of diarrheal cases. The subsequent inclusion of the folk term significantly improved the program's impact (Scrimshaw and Hurtado 1988). Attempts will be made during the pilot phase to assess the cultural perception of diarrheal illness and to elucidate the folk terminology and basic local illness beliefs about diarrhea (Appendix L). We conducted similar studies in previous research to obtain and validate local folk terms for diarrheal illness that resemble most closely the biomedical definition for diarrheal illness mentioned previously (Mausezahl 1996, Pitts et al. 1996).

A start of a new episode of diarrhea will be defined as the first day of diarrhea that occurs after at least three consecutive diarrhea-free days. Similarly, the end of an episode is determined by the onset of three consecutive diarrhea-free days. Our choice of three rather than some other number of disease-free days is based on the work of Morris *et al* who modelled the sensitivity of different definitions of diarrheal episodes and described the definition we

have chosen as ideal in situations of medium to high incidence (specifically greater than six trigger events/child/year) allowing for different lengths of duration and within-child clustering (Morris et al. 1994). Persistent diarrhea is defined as an episode lasting longer than 14 days according to WHO standards (Anonymous 1988); diarrhea episodes of shorter duration will be defined as "acute".

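### The diary chart counts stools from sunrise to sunset, the case definition needs a 24-hour count, and the protocol contradicts itself on whether diary or interview supplies the episode count

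*Protocol*

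**What the plan says.** Protocol section D.4 sets the case definition for the whole trial: "a 24 hours period with three or more non-bloody loose or liquid motions, or one or more bloody, loose or liquid motions". A new episode needs three diarrhea-free days before it.

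Section D.6.c says that the main outcome is "cluster(village)-level incidence rates of diarrheal episodes through two monitoring procedures for the entire 12 month follow-up period". The first procedure is a calendar that mothers will be given for daily entries. Of that calendar it says "This chart was pre-tested among 11 households in our pilot study in Mizque", and it lists among the items recorded "The number of bowel movements (from sunrise to sunset), color and consistency of the stool". The second procedure is a weekly fieldworker visit with a standardized questionnaire. On what the visit assesses, it says "This includes frequency of bowel movements and the presence of other symptoms (fever, vomiting, dehydration"; no counting window is stated for the motions.

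On which source leads, the Project Summary says that the data come from "morbidity diaries kept by mothers and validated through weekly home visits". Section C.2 says the reverse of the diary: "This serves to validate our weekly diarrheal morbidity assessment through a maternal interview".

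**The concern.** The threshold of three motions applies to 24 hours. A chart that stops at sunset leaves night motions out of the count, so a child with two loose motions by day and one by night meets D.4 but not the chart. The three-day separation rule needs a classification for each day, and the diary is the instrument described as a daily record. No section adds night motions to it.

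The absolute quantities are at stake: incidence, the rate difference and episodes averted (D.6.d), days with diarrhea and mean duration (D.6.c), and cost per episode averted (D.6.e). The contradiction about the leading source adds to this, because the two sources may use different windows and so give different counts for the same child.

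**Working it through.** **1. Windows side by side.** D.4: 24 hours, at least three non-bloody motions or at least one bloody motion. Diary in D.6.c: sunrise to sunset. Weekly questionnaire in D.6.c: frequency of motions with no window, although the same paragraph gives urinations a 24-hour window. The first two conflict and the third is open.

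**2. The plan's own figure.** Inputs from D.8: rates R0 = 5 and R1 = 3.333 per child-year, z-values 1.96 and 0.84, y = 10 person-years per cluster, k = 0.2.

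c = 2 + (1.96 + 0.84)² × {(R0 + R1)/y + k²(R0² + R1²)}/(R0 − R1)²
= 2 + 7.84 × (0.833 + 1.444)/2.778 = 8.43, so 9 per arm. This agrees with the text of D.8, which then raises the number to 11.

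**3. Effect of an undercount.** Assumption: the same share s of episodes is detected in both arms, with no false positives. Both rates are multiplied by s, so the intervention-to-control ratio stays at 3.333/5 = 0.667.

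| s | recorded rates | difference | clusters per arm, y = 10, k = 0.2 | clusters per arm, y = 30, k = 0.2 |
|---|---|---|---|---|
| 1 | 5.00 v 3.33 | 1.67 | 8.43 | 6.86 |
| 0.8 | 4.00 v 2.67 | 1.33 | 9.02 | 7.06 |
| 0.7 | 3.50 v 2.33 | 1.17 | 9.44 | 7.20 |
| 0.5 | 2.50 v 1.67 | 0.83 | 10.78 | 7.64 |

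With the planned 30 children for 12 months (y = 30), the requirement stays well below 11. At k = 0.3, the upper bound in D.8, it is 11.96 with full detection and 12.29 at s = 0.7. The shortfall against 11 is there already, and the undercount adds about 0.3 of a cluster.

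For a fixed programme cost, cost per episode averted scales as 1/s: at s = 0.7 it is 1/0.7 = 1.43 times the value under full detection.

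**4. Day level, if the diary alone classified days.** Assumption: each motion falls in daylight independently with probability q. The documents give no value, so q = 0.6 to 0.8 is illustrative. The probability that a non-bloody qualifying day still shows three or more motions is the binomial tail P(X ≥ 3) with n motions in 24 hours:

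| n | q = 0.6 | q = 0.7 | q = 0.8 |
|---|---|---|---|
| 3 | 0.22 | 0.34 | 0.51 |
| 4 | 0.48 | 0.65 | 0.82 |
| 5 | 0.68 | 0.84 | 0.94 |

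**5. Episode level.** One qualifying day registers an episode. For three independent days, P(kept) = 1 − (1 − P)³. At q = 0.7 this is 1 − (1 − 0.343)³ = 0.72 with three motions a day and 1 − (1 − 0.652)³ = 0.96 with four. Episodes are therefore lost less often than days. Three consecutive missed days inside an episode work the other way, because they split it into two and raise the count. Bloody diarrhea needs one motion and is affected less.

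**The case against.** A reader might infer that the primary outcome itself misses diarrhea days, or that night stools are never counted. The documents do not support that. D.6.c draws the outcome from two procedures, and after describing the weekly visit it says the outcomes rest on 52 measurements. D.5 likewise counts 52 recording sheets per child, and section A has field staff recording daily measurements each week. If the interview classifies episodes, as C.2 implies, the diary window need not touch the primary count. The sentence with the daylight window is in the past tense and describes the pilot, and C.2 says that final instruments are still being developed.

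These points limit the claim but do not remove it. The pre-tested chart is identified with the calendar that mothers will be given, no other chart is described, and the introduction plans to use the pretested diaries in the eight-week baseline survey that pairs villages. The interview states no window and no day-by-day stool count.

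A reader might also infer a biased rate ratio or a serious loss of power. Under equal undercount neither follows (steps 2 and 3). Nor do the documents show that the source would be chosen after seeing the data: a rule for combining the two sources may stand in a statistical analysis plan that is not at hand. The opposite statements within the protocol still need correcting.

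**Conclusion.** The point holds in a limited form. The diary window conflicts with the D.4 definition, and where the diary classifies days it can miss non-bloody days near the threshold. The Project Summary and C.2 contradict each other on which source leads.

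The consequences are confined to absolute quantities as long as both arms undercount equally, which is an assumption. The fall in the difference from 1.67 to 1.17 illustrates 70% detection and is not an estimate. Days with diarrhea and duration are affected more directly than the episode rate, because each missed day counts against them. For the episode count, lost and split episodes pull in opposite directions, so neither the size nor the net direction can be derived from the documents. The change is still worth making, because it is cheap now and night motions that go unrecorded cannot be recovered reliably later.

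**What to change.** Change the diary to a full 24-hour count, for example by adding a night box that the mother fills in each morning, and state the same 24-hour window in the weekly questionnaire. Reconcile the Project Summary, C.2 and D.6.c by naming one source for the primary episode count and giving the other a checking role, before follow-up starts and preferably before the baseline survey. Either source is defensible; the text leans both ways, and what matters is that one is fixed.

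The cost is small: one pictorial form redrawn, translated and back-translated, a brief re-test of the new box, and ethics clearance together with the instruments that C.2 says are still to be submitted. A few sentences of the protocol change, and mothers make one more entry each day.

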#### D.6.d. Estimation of diarrheal disease preventive fraction of child-diarrheal illness.

Applying the definition of Last, community effectiveness is defined in this setting as the impact of the SODIS intervention on the overall incidence rate of child diarrhea in the community (Last 1995). It can be expressed in two ways:

- i.) The relative risk (the ratio of the risk of diarrhea in the intervention group to that in the control group). With this ratio the community protective effect ( $CPE = (1-RR) \times 100$ ) can be obtained which expresses the percent reduction in the overall diarrheal incidence rate as a result of the SODIS intervention.
- ii) The number of diarrheal illnesses averted as a result of the intervention (attributable risk) is measured by the difference in incidence density rates between the two study groups. To obtain an absolute number of diarrheal illnesses prevented by the use of SODIS, we multiply the attributable risk with the number of diarrheal cases obtained from the cross-sectional study. (In this calculation we assume that the results from the 22 cross-sectional studies represent the frequency of diarrheal illness in the general population).

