## D.5. Evaluation of the outcome measures

Evaluation of differences in the primary outcome measure between the active and control arms will be through relative incidence rates of gastrointestinal illness (total episodes of child diarrhea / total person-time of observation in the control group divided by the same measure in the active group) adjusted for the nature of the cluster sampling. Secondary outcomes include child-level outcome measures such as the total number of days with diarrhea, the mean duration of diarrhea, and the number of visits to health care providers caused by the diarrhea. We also will obtain information to allow an analysis using a combination of symptoms that describe 'highly credible gastrointestinal illness' (HCGI) (Payment et al. 1991) from our weekly diarrhea monitoring household interviews (Appendix J).

Outcome data will be collected through a surveillance system established to measure diarrheal morbidity through daily illness diaries kept by the mother/caretakers of the children, and through weekly home-visits by project staff. A standardized questionnaire will be administered covering the clinical signs and gastrointestinal symptoms of current illness. Environmental (household and village-specific characteristics) as well as behavioral traits (water and food handling practices in the home, presence of pets, latrine arrangements) will also be recorded. Weekly home visits result in a total of 52 environmental and morbidity recording sheets for each child in the study.

Stool specimens will be collected and submitted for microbiologic analysis from a sub-sample of 220 (33%) of the children in the study during baseline, at their first diarrheal episode. In addition, as suggested by the reviewer, the entire sub sample will also be re-examined at a fixed time (at 6 months of follow up). This will allow us to measure three additional pathogen-specific outcomes: the prevalence of asymptomatic infections; the proportion of diarrhea attributable to infection for each organism detected in the study; and differential (pathogen-specific) infection rates in intervention and control group.

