#### D.6.e. Assessing the cost-effectiveness of SODIS and estimating the social and economic impact of SODIS at household level.

We will use cost-effectiveness analysis to complete this objective. Cost-effectiveness analysis compares the net monetary costs of a health care intervention with a measure of clinical outcome or effectiveness such as mortality rates, life years saved or events averted.

The aim is to estimate the unit cost for averting 1 (one) episode of diarrhoea by SODIS. Further we will perform a cost description of the net savings for a household per episode of diarrhoea averted. Multiplying this figure with the preventive fraction obtained from Section D.e we will generate a specific measure of economical and social impact of the SODIS intervention.

Costs will be assessed from the perspectives of the household. Household costs for a diarrhoeal episodes will be determined through a convenient sample of 50 acute and 50 persistent/severe episodes. The following parameters of the participating households will be assessed: a.) *direct costs* for medication, care services, or transportation, and b.) *indirect costs* of caretaker-time lost from work from caring for the sick child, d.) *time lost* for transportation and e.) time lost for a visit (waiting and treatment). Daily logs will be maintained by the household to measure these indicators. We will use local estimates of hourly income for a economically productive women to estimate the hourly wage of the mothers/caretakers. Programme costs for the total episodes of diarrhoea averted by the intervention will include the following costs: a.) for community building/training for the use of SODIS, b.) for actual costs of the SODIS bottles and their handling (e.g. cleaning before distribution), c.) the distribution, and d.) replacement of broken bottles. Research costs will be excluded.

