## D.8. Sample size calculation

Sample size calculations were designed for the trial to detect a 33% absolute reduction in the annual diarrheal incidence rate in children below the age of 5 in SODIS users compared to non-users. We consider a reduction of the annual incidence of 5 to 3.33 episodes per child <5 as of significant public health importance (Bern et al. 1992). This absolute rate reduction (1.67 episodes/child/year) is even lower than what was found in the Kenyan SODIS trials (2.1 epi/ch/yr)(Conroy et al. 1999). Conroy observed 2546 diarrhoeal episodes among a total of 4382 fortnight observation periods (58.1%) in the control group (172 children). A total of 2210 episodes among 4323 observations (48.8%) were found in the intervention group (174 children) resulting in their report of a 9.3% reduction of diarrhoea in children below 6 years. By considering 26 repeated measurements of fortnight periods an approximation of the annual incidence, the Conroy findings suggest an average annual reduction of 2.1 episodes/child/year for a child in the control *versus* intervention group (14.6 *versus* 12.7 epi/ch/yr). The magnitude of diarrhea reduction we have powered the study to detect compares favorably to the achievements of other well designed interventions that influenced national diarrheal disease control programs elsewhere in developing countries (Huttly et al. 1997, Stanton and Clemens 1987).

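### The rule in D.6.d for the number of illnesses prevented multiplies a rate difference by a case count, which is not a count of cases, and D.5 states the primary rate ratio in the opposite direction to D.6.d and D.9

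*Protocol*

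**What the plan says.** **Number prevented.** Protocol D.6.d, point ii, says that the attributable risk "is measured by the difference in incidence density rates between the two study groups". For an absolute number of illnesses prevented it continues: "we multiply the attributable risk with the number of diarrheal cases obtained from the cross-sectional study". It assumes that the 22 cross-sectional studies represent the general population. D.6.b, however, describes the baseline as a prospective eight-week survey that replaced an earlier 7-day cross-sectional one.

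**Episodes prevented in the cost analysis.** D.6.e takes the number of episodes prevented as the difference between the episodes observed in the two arms, and gives D.6.d as the source.

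**Ratio and percent reduction.** D.6.d, point i, defines the relative risk as "the ratio of the risk of diarrhea in the intervention group to that in the control group". From it comes CPE = (1 − RR) × 100, "which expresses the percent reduction in the overall diarrheal incidence rate as a result of the SODIS intervention". The regression in D.9 also returns treatment relative to control. D.5 defines the primary measure the other way round, as episodes over "total person-time of observation in the control group divided by the same measure in the active group".

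**The concern.** A difference in incidence densities has the unit episodes per child-time. It becomes a number of episodes only when multiplied by child-time. Multiplied by a number of episodes, it gives a quantity with no interpretation, whose value depends on whether rates are expressed per year, month or week. A case count needs a proportion as its multiplier, and D.6.d already has one: 1 − RR.

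The number prevented is a public-health figure. D.10 says that cases averted can be combined with implementation cost, and the introduction says that results will go to the programme and the Bolivian government for rapid decisions. D.6.d and D.6.e give two rules for this figure under one cross-reference, so an analyst cannot tell which applies.

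The direction of the primary ratio is a separate matter. With two opposite definitions, a reported ratio of 1.5 or 0.67 cannot be read without knowing which section was followed.

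**Working it through.** **Inputs**
- Control rate 5 and intervention rate 3.33 episodes per child-year (D.8: "We consider a reduction of the annual incidence of 5 to 3.33 episodes per child <5 as of significant public health importance").
- 660 children, 330 per arm (D.6.c); eight-week baseline survey (D.6.b); plausible control rate 4 to 5 per child-year (D.8).
- Assumption: all 660 children are observed for eight full weeks at 5 episodes per child-year. The Protocol gives neither the number of survey children nor a case count.

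**1. The plan's own figure**
5 − 3.333 = 1.667 per child-year, and 1 − 3.333/5 = 33.3%. Both match D.8 (1.67 and 33%).

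**2. The D.6.d rule for any N**
Rule: rate difference × N = 1.667 × N in annual units, or 167% of all cases.
Valid: (1 − RR) × N = 0.333 × N.
Rule divided by valid = N / child-time, which is the baseline rate in the chosen unit. Per child-year this is 5; per child-month it is 5/12 = 0.42.

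**3. Illustration under the assumption**
Child-time = 660 × 8/52 = 101.5 child-years.
Cases N = 101.5 × 5 = 507.7.
Valid count = 1.667 × 101.5 = 169.2, and equally 0.333 × 507.7 = 169.2.

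| Rate expressed per | Rate difference | Rule: difference × 507.7 |
|---|---|---|
| child-year | 1.667 | 846 |
| child-month | 0.1389 | 70.5 |
| child-week | 0.0321 | 16.3 |
| child-day | 0.00457 | 2.3 |

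None of these equals 169.

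**4. When the rule exceeds all cases**
In annual units this happens whenever the rate difference is above 1. At 5 per child-year that is any reduction above 1/5 = 20%; at 4 per child-year, any reduction above 1/4 = 25%.

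**5. The rule stated in D.6.e**
With 330 child-years in each arm: 330 × 5 − 330 × 3.333 = 1,650 − 1,100 = 550, which equals 1.667 × 330. It is correct when child-time is equal. The D.6.d rule applied to the 1,650 control episodes would give 1.667 × 1,650 = 2,750.

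**6. Ratio direction**

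| True reduction | Intervention/control | CPE | Control/active (D.5) | CPE if this ratio is used |
|---|---|---|---|---|
| 20% | 0.80 | +20% | 1.25 | −25% |
| 33.3% | 0.667 | +33.3% | 1.50 | −50% |
| 50% | 0.50 | +50% | 2.00 | −100% |

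**The case against.** The case for leniency is strong on consequences, and most of it stands.

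- **Cost-effectiveness.** A reader might infer that the faulty product becomes the denominator of the cost-effectiveness ratio. The text does not support that. D.6.e states its own rule, which is sound with equal child-time. What remains is a conflict between two rules under one cross-reference.
- **Percent reduction.** A reader might infer that following the Protocol makes a benefit look like harm. D.6.d prints the correct ratio beside the CPE formula, and D.9 returns the same direction. The −50% arises only if the D.5 ratio is substituted.
- **Five times too large.** This holds only per child-year. D.6.d fixes no time unit, and D.6.c is headed with monthly incidence. Per child-month the rule understates the valid figure.
- **D.6.e savings.** A reader might see a second error in "Multiplying this figure with the preventive fraction obtained from Section D.e we will generate a specific measure of economical and social impact". Savings per episode averted times the preventive fraction is a valid quantity: the expected saving per episode that would otherwise occur. The text promises a measure of impact, not total savings. The section reference is garbled, but no error of method is shown.
- **Aims.** The five specific aims do not list an absolute number averted. The preventive fraction, which the Project Summary does list, is handled correctly in D.6.d, point i.

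None of this rescues the product in D.6.d, point ii. Reading attributable risk there as a proportion is ruled out, because the same point defines it as a difference in incidence densities. Nor does it reconcile D.5 with D.6.d and D.9.

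**Conclusion.** The concern holds for two statements.

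First, the rule in D.6.d, point ii, does not yield a number of illnesses prevented. At the design rates and in annual units it returns 167% of all cases where 33% is right. That ratio depends on the unit but not on N. The figures 846, 70 and 169 rest on the assumption of 660 children, eight full weeks and 5 episodes per child-year. D.6.e gives a different rule while citing D.6.d, and the two must be reconciled.

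Second, D.5 defines the primary ratio inversely to D.6.d and D.9. This is an inconsistency in the definition of the primary measure, with a possible sign error in the reported reduction. The CPE formula itself is right.

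The primary hypothesis test, the sample size and the randomization are untouched. This is a correction to reported quantities, to be made before analysis.

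**What to change.** - **D.6.d, point ii:** define cases averted as rate difference × child-time at risk in the target population, with both in the same time unit. Equivalently, use (1 − RR) × cases expected without the intervention. Take baseline cases and child-time from the eight-week survey in D.6.b, and replace the reference to cross-sectional studies.
- **D.6.e:** use the same rule for episodes prevented, so that unequal child-time between arms is accounted for.
- **D.5:** define the primary ratio as intervention over control, in line with D.6.d and D.9.

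The cost is a few sentences. No new data, no change to the design and no change to the primary test are needed.
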